## Abstract

**Background:**

Smoking during pregnancy is harmful to the unborn child. Few smoking cessation interventions have been successfully incorporated into standard antenatal care. The main aim of this study is to determine the feasibility of a personal financial incentive scheme for encouraging smoking cessation among pregnant women.

**Design:**

A pilot randomised control trial will be conducted to assess the feasibility and potential effectiveness of two varying financial incentives that increase incrementally in magnitude ($20 vs. $40AUD), compared to no incentive in reducing smoking in pregnant women attending an Australian public hospital antenatal clinic.

**Method:**

Ninety (90) pregnant women who self-report smoking in the last 7 days and whose smoking status is biochemically verified, will be block randomised into one of three groups: a. No incentive control group (n=30), b. $20 incremental incentive group (n=30), and c. $40 incremental incentive group (n=30). Smoking status will be assessed via a self-report computer based survey in nine study sessions with saliva cotinine analysis used as biochemical validation. Women in the two incentive groups will be eligible to receive a cash reward at each of eight measurement points during pregnancy if 7-day smoking cessation is achieved. Cash rewards will increase incrementally for each period of smoking abstinence.

**Discussion:**

Identifying strategies that are effective in reducing the number of women smoking during pregnancy and are easily adopted into standard antenatal practice is of utmost importance. A personal financial incentive scheme is a potential antenatal smoking cessation strategy that warrants further investigation.

**Trial registration:**

Australian New Zealand Clinical Trials Registry (ANZCTR) number: ACTRN12612000399897

## Background

### Smoking during pregnancy is a major public health issue

Smoking rates during pregnancy vary considerably, within and between countries
[1-4]. For example, recent data illustrates large variations in smoking rates at the end of pregnancy across England, ranging from 3% to 30%
[4]. Similarly, the European perinatal health report have detailed smoking rates during the second trimester from 5% in Lithuania to 22% in France
[2]. In 2009, approximately 15% of Australian women smoked during their pregnancy
[3]. Rates are known to be higher in certain subpopulations such as lower socioeconomic, indigenous and ethnic minority groups
[1,5]. Smoking during pregnancy is directly associated with a number of serious, harmful effects to the baby, including preterm delivery, low birth weight and perinatal mortality
[6,7]. Babies born to mothers who smoke during their pregnancy are also more likely to require special care or neonatal intensive care compared to mothers who do not smoke
[6].

### Current prenatal smoking cessation interventions are often not adopted into standard care

Despite a recent Cochrane review
[8] reporting an absolute difference of 6% reduction in smoking in late pregnancy following cessation interventions, very few are adopted into standard care. Furthermore, pregnant women who do continue to smoke may not receive support to quit
[9]. For example, one Australian study found that almost three-quarters of pregnant smokers in one hospital did not receive smoking cessation advice at 30 weeks gestation
[9]. Time restraints, competing pressures, staff attitudes, lack of training or skill, administrative barriers and lack of acceptable interventions for women and staff were identified as some of the barriers affecting implementation of smoking cessation into standard antenatal care
[5].

### Difficulties in accurately verifying women’ smoking status

Due to social stigma and social desirability, women often underreport their current smoking behaviour, making it difficult for clinic staff to accurately verify women’s smoking status
[1]. For example a recent study indicated underestimations of self-reported smoking status during pregnancy by as much as 25%
[10]. The incorporation of simple, rapid, biochemical validation methods of patients’ smoking status, may help to overcome this problem. For instance, a study of family practice patients illustrated validity in using a semi-quantitative dipstick assay (NicAlert®) to rapidly asses participant smoking status through saliva cotinine analysis
[11]. This study illustrated high sensitivity (99%) and high specificity (96%) of the simple, 20-minute analysis of saliva cotinine
[11].

### Contingent reinforcement is an appropriate strategy for health behaviour change

The use of a contingent reinforcement schedule, such as a Personal Financial Incentive (PFI), whereby individuals are provided a monetary reward for their engagement in a particular behaviour, may be an effective strategy to assist in reducing smoking behaviour. Contingent reinforcement has strong theoretical grounding within behavioural psychology and more specifically the theory of operant conditioning
[12]. The lack of relevant health promotion theories being applied to current smoking cessation interventions for pregnant women has been identified as a general criticism of interventions conducted in this area
[5]. Contingency management is based on the notion that because behaviour is reinforced by its consequences it can be modified by changing the consequences
[12]. There are several guiding principles of contingency management suggested as potentially relevant in treating substance use
[13,14] and additional principles which have been identified as effective to PFI by previous literature reviews
[15,16]. These include the use of: behavioural contracting; positive reinforcements; frequent and immediate feedback and rewards; and incentives of sufficient and incremental magnitude
[14]. The use of financial incentives also has a strong theoretical and empirical grounding in economics, where the monetary transfer influences the ratio of benefits to costs, that in turn influences choice and decision making.

Contingency management approaches have been successfully applied to other health behaviours and several have been effectively translated into real world practice
[17]. For example, rewards or reduced premiums have long been utilised by health insurers in the United Kingdom and South Africa to encourage individuals to engage in health promoting behaviours, such as exercise or screening programs
[16]. In Australia the Government has successfully incorporated incentive-based programs to influence several health behaviours including, immunisation and population growth
[18-20]. These programs resulted in an increase in child immunisation rates from 56% in 1996 to 90% in 2003
[20]; and a significant rise in fertility rates
[18,19]. Additionally, the results from one state-based study found no significant differences in fertility rates of socially disadvantaged groups compared to non-disadvantaged groups
[19]. The success of such financially based incentives introduced by the government to influence health behaviours provides a strong platform for how a similar program to reduce smoking in pregnant women could be introduced into practice, if found feasible and effective.

### Contingent reinforcement has been found to be effective in facilitating smoking cessation

A recent Cochrane review assessing smoking cessation interventions in pregnant women found that interventions that included an incentive component resulted in a significantly larger effect in point-prevalence abstinence during late-pregnancy, compared to other intervention strategies
[15]. Though PFI seems to be a potentially effective method in promoting smoking cessation in pregnant women, very few studies have assessed their effectiveness among pregnant smokers in an Australian antenatal care setting. Additionally, there have been no Australian studies which have assessed the effect of reward size on smoking cessation behaviour. One recent descriptive study found pregnant women had mixed and often unfavourable views regarding the acceptability and potential effectiveness of using PFIs to assist women to quit smoking
[21]. However, a significantly higher percentage of smokers reported favourable views on the use of PFI for smoking cessation, highlighting the ambiguity surrounding the acceptability and potential benefit of such a strategy
[21]. Consequently, it is important that research is conducted which aims to assess whether a PFI smoking cessation program is feasible in an Australian antenatal care setting.

### Aims

The primary aim of this study is to test the feasibility of a personal financial incentive (PFI)-based intervention at encouraging smoking cessation in pregnant women attending an Australian public hospital for antenatal care. Specifically, the study will assess: (i) consent rates of women to participate in the trial; (ii) loss to follow-up rates of study participants; (iii) compliance with saliva cotinine and hair cotinine analyses for biochemical validation (iv) acceptability of using a touchscreen computer for self-reported smoking status and demographics; (v) acceptability of saliva cotinine and hair cotinine analyses for biochemical validation of smoking status; (vi) acceptability of incentives of varying magnitude ($20 vs. $40) to staff and study participants; and (vii) the perceived barriers and facilitators to using financial incentives in a public antenatal clinic among clinic staff. Additionally, secondary aims include: (i) to assess the potential effectiveness of the varying PFI amounts ($20 vs. $40) in reducing smoking among study participants; (ii) to assess the accuracy of self-report smoking status with saliva and hair cotinine analysis; and (iii) to undertake a cost-effectiveness analysis comparing the changes in costs of the intervention and changes in quit rates between each arm of the trial.

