[36]. The PHQ-2 has evidence of criterion validity; as well as acceptable specificity (92%) and sensitivity (83%)
[35]. Previous research has found a relationship between depression and smoking status
[37,38].

• *Economic questions*: Women will be asked to a number of questions relating to their personal out-of-pocket costs, time costs and health care utilisation incurred as a result of the intervention.

• *Social characteristics*: women will be asked whether their partner or others within their household smoke.

*Follow*-*up surveys*: During each of the follow-up visits, women will be asked to complete a brief touchscreen computer survey using a number of items from the baseline survey. Questions will assess their current smoking status, number of cigarettes smoked per day (if they have not abstained), changes in smoking behaviour, partners’ current smoking status, exposure to environmental smoke, the number of quit attempts made, gestation age; the PHQ2 and efforts to engage with quit smoking support services.

The following two biochemical analyses will be used to validate women’s self-reported smoking status:

1. *Saliva cotinine analysis*: will be used to biochemically validate self-reported smoking status for all participants at baseline and each of the eight intervention sessions using the NicAlert® semiquantitative dipstick assay. A previous study analysing 167 family practice patients using NicAlert® illustrated acceptable levels of sensitivity (99%) and specificity (96%)
[11].Cotinine analysis with the NicAlert® dipstick takes approximately 20 minutes and can be performed by untrained persons, highlighting the potential utility of such a test in clinical practice .

2. *Hair cotinine analysis*: will be undertaken during the eighth or final intervention session. Participants will be asked to provide a small sample of hair taken from the nape of the neck. Samples will be transported to an off-site laboratory for analysis. Hair cotinine analysis can reliably quantify long-term exposure to tobacco, with each centimetre of scalp hair representing approximately 1 month of past exposure
[39]. Gas chromatography – mass spectrometry will be used to analyse hair cotinine levels, as it is considered the standard reference in analysis of cotinine
[40]. A cut-point of 0.2 ng/mg has been found to distinguish between pregnant active smokers and passive or unexposed with high levels of sensitivity (91%), specificity (94%) and test accuracy (91.7%)

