[40]. We will also validate hair cotinine analysis as a measure of smoking status by comparing its accuracy against women’s self-report smoking status and saliva cotinine throughout the study.

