#### Validation analysis of saliva and hair cotinine compared to self-report smoking rates

Agreement between self-reported smoking status and the cotinine saliva test strip will be assessed using the Kappa statistic. Agreement between self reported smoking status and hair cotinine results will also be assessed using the Kappa statistic.

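### Secondary aim (ii) asks how accurate self-reported smoking is, but the only planned statistic, kappa, cannot give the share of false abstinence claims or separate misreporting from test error

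*Protocol article*

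**What the plan says.** The Aims section of the Protocol article lists as secondary aim (ii) "to assess the accuracy of self-report smoking status with saliva and hair cotinine analysis". The section on validation analysis names one statistic for each test. For saliva: "Agreement between self-reported smoking status and the cotinine saliva test strip will be assessed using the Kappa statistic". For hair: "Agreement between self reported smoking status and hair cotinine results will also be assessed using the Kappa statistic". It names no other measure, benchmark or threshold.

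The article gives the error rates of both tests. For saliva, the Background states: "This study illustrated high sensitivity (99%) and high specificity (96%) of the simple, 20-minute analysis of saliva cotinine". Secondary outcome measures repeats these figures and adds that they come from 167 family practice patients. For hair, the same section gives sensitivity 91%, specificity 94% and accuracy 91.7% at a cut-point of 0.2 ng/mg.

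Two further statements matter. Hair is itself to be checked against self-report and saliva: "We will also validate hair cotinine analysis as a measure of smoking status by comparing its accuracy". Hair also looks back over a long period, "with each centimetre of scalp hair representing approximately 1 month of past exposure", whereas Procedures asks women at each session about the last 7 days.

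**The concern.** Accuracy of self-report has a direction. The reader wants to know how many women who say they have stopped are still smoking and, less often, how many admitted smokers test negative. Kappa merges both kinds of disagreement into one number, gives neither proportion, and changes with the proportion of smokers even when reporting behaviour and test quality stay the same.

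An imperfect test also produces disagreement when every report is true. Without a benchmark for that, a hair kappa well below 1 could be taken as a sign of misreporting. The Background makes that reading easy, because it cites underreporting of up to 25% and offers biochemical testing as a possible remedy. At stake is the answer to one secondary aim, which may inform how smoking status is verified in later work. The primary feasibility outcomes are not affected.

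**Working it through.** **Inputs from the article.** Saliva: sensitivity (Se) 0.99, specificity (Sp) 0.96. Hair: Se 0.91, Sp 0.94.

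**Inputs assumed.** The proportion π of women smoking at the session analysed is set at 60%, 75% and 90%; the article gives no such figure. Self-report and test are first taken to cover the same period.

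**The plan's own figure.** The article states no expected kappa. The nearest stated figure is the hair accuracy of 91.7%. Accuracy = Se·π + Sp·(1 − π), so 0.917 = 0.91π + 0.94(1 − π) gives π = 0.023/0.03 = 0.77. The figure fits 91% and 94% if about 77% of the source sample smoked. The article does not give that mix, so the figure is consistent with its inputs but cannot be reproduced from them alone.

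**Disagreement from test error alone, every report true.**
- Abstinence claims contradicted = 1 − Sp: saliva 4%, hair 6%.
- Admitted smokers testing negative = 1 − Se: saliva 1%, hair 9%.

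The first pair applies to women claiming abstinence, the second to women admitting smoking. Neither applies to all women.

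**Kappa under fully honest reporting.**
- Observed agreement: po = π·Se + (1 − π)·Sp
- Proportion testing positive: t = π·Se + (1 − π)(1 − Sp)
- Chance agreement: pe = π·t + (1 − π)(1 − t)
- Kappa = (po − pe)/(1 − pe)

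Hair at π = 0.90: po = 0.819 + 0.094 = 0.913; t = 0.819 + 0.006 = 0.825; pe = 0.7425 + 0.0175 = 0.760; kappa = 0.153/0.240 = 0.64.

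| Assumed proportion smoking | Hair kappa | Saliva kappa |
|---|---|---|
| 60% | 0.840 | 0.954 |
| 75% | 0.794 | 0.953 |
| 90% | 0.638 | 0.929 |

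The hair kappa falls by 0.20 across the range although nobody misreports and the test is unchanged. The saliva kappa hardly moves.

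**Effect on the directional proportion, saliva.** If a share f of abstinence claims is false, the share contradicted is f·Se + (1 − f)(1 − Sp).
- f = 5% (assumed): 0.0495 + 0.0380 = 8.75%, about 1.75 times the truth.
- f = 25% (borrowed from the Background only as an illustration, since its denominator differs): 0.2475 + 0.0300 = 27.75%, about 1.1 times the truth.

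Test error therefore matters most when misreporting is rare.

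**How many claims there will be.** If 90 women are recruited and 20% drop out, 72 reach the final session. With 10% to 40% abstinent (the complement of the assumed prevalences), that gives about 7 to 29 claims. By test error alone, saliva would contradict 0.04 × 7.2 = 0.3 to 0.04 × 28.8 = 1.2 of them.

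**The case against.** The strongest reply is that the article makes no mistake here. It prints the tests' error rates, chooses a measure that takes neither method as the truth, and plans to validate hair against self-report and saliva. A reader might infer that the plan treats the tests as error-free, or counts every disagreement against the woman. The text does not support either reading. Nor does it contain a threshold or decision rule by which a low kappa would lead to a finding that self-report is unreliable.

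A second reply is that the size is selective. The hair range of 0.64 to 0.84 does not follow from the article's error rates alone, because it also needs the assumed prevalences. For saliva, the test used at every session, the effect on kappa is small. Both points stand.

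A third reply concerns the remedy. It is tempting to correct the share of false claims for test error in both tests. For hair this would be unsound. Hair looks back about a month per centimetre and the report covers 7 days, so a woman who stopped recently and says so truthfully can test hair-positive. The correction would count her as a false claimant. For the same reason, 6% cannot be offered as the hair figure expected under honest reporting, and the true honest-reporting hair kappa could be lower than in the table. With so few claims, corrected estimates would also often be negative. For example, with 15 honest claims, hair contradicts none with probability 0.94^15 = 0.40, and the corrected share is then (0 − 0.06)/(0.91 + 0.94 − 1) = −7%.

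The last reply is that adjustment for an imperfect reference belongs in a statistical analysis plan. That is fair, and its absence from the article is not the point. The article does name the statistic for this aim, and that statistic does not answer it.

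**Conclusion.** The point holds as a mismatch between aim and statistic. The aim is accuracy of self-report; the named analysis is symmetric agreement, which gives neither the share nor the direction of wrong reports and cannot separate misreporting from test error. Hair and self-report are also each used to check the other, and kappa cannot say which is at fault.

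Under fully honest reporting the hair kappa would be about 0.84 to 0.64 for 60% to 90% smoking, and the saliva kappa about 0.95 to 0.93. This rests on the quoted error rates carrying over to these women, on the assumed prevalences and, for hair, on matching time windows, which the article's own description contradicts. For kappa the concern is mainly hair. It is a worthwhile and cheap improvement to a secondary aim of a pilot, and not an error that undermines the trial.

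**What to change.** Keep kappa for both tests as a description of agreement, and add the following.

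- **Saliva**, the test closest in time to the 7-day report: the proportion of abstinence claims contradicted by the test and the proportion of admitted smokers testing negative, each with a 95% confidence interval. Print beside them the values expected from test error alone, about 4% and 1%. State that these hold only if the quoted specificity and sensitivity apply at the cut-point used: Procedures takes level 0 as negative, and the article does not say which cut-point gave 96%. Also give the kappa expected under honest reporting at the observed prevalence.
- **Error-corrected share of false claims**, (observed − (1 − Sp))/(Se + Sp − 1): for saliva only, as a sensitivity analysis over a range of error rates.
- **Hair**: report disagreement in each direction without correction. State that hair reflects about one month per centimetre, so an honest recent quitter can test positive and disagreement with a 7-day report is not evidence of misreporting.

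The cost is analysis wording only; all the data are already to be collected. The downside is imprecision, because abstinence claims will be few and the intervals wide. The error rates come from other populations, so the benchmarks are approximate.

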## Methods/design

### Study design

This is a proof-of-concept trial that will employ a randomised control trial design to assess the potential efficacy of personal financial incentives on pregnant women smoking cessation rates; combined with a qualitative analysis to investigate the acceptability of the intervention to participants and clinic staff. The study will involve a baseline survey; eight intervention sessions; and a post-intervention telephone interview of participating women and semi-structured interviews with clinic staff. Self-reported smoking status will be validated through saliva cotinine analysis using NicAlert® semi-quantitative dipstick assay. Continuous or long-term smoking cessation will be additionally assessed through hair analysis of patient’s cotinine levels using gas chromatography – mass spectrometry.

### Setting

The study will take place at the antenatal clinic within a large public teaching hospital in New South Wales, Australia. The antenatal clinic operates a 5 days-a-week service with most women presenting for an average of 6 to 8 clinic visits over the course of their pregnancy. The hospital manages approximately 4,300 deliveries each year with the majority of these women receiving antenatal care predominantly through the hospital antenatal clinic.

### Participants

A sample of ninety (90) consenting pregnant women will be recruited to participate. Women will be considered eligible if they are: (1) aged at least 16 years; (2) presenting for their first antenatal visit; (3) less than 31 weeks gestation; (4) sufficient in English language to complete the survey; and (5) a current smoker (defined as having smoked in last 7 days and a return a positive saliva sample for cotinine). Pregnant women will be ineligible to participate if they have elected to receive shared antenatal care with their GP and/or are considered by clinic staff to have a severe cognitive or psychiatric disorder; currently being treated for chemical dependency other than alcohol or tobacco; or have quit smoking before their first antenatal appointment.

